### Secondary outcome analysis

#### Pain scores

The secondary outcome of the change in pain scores (measured with VAS) from baseline to 30 min in patients with “suspected renal colic” will be compared between the two trial arms using the Mann-Whitney *U* test. The change in pain scores (measured with VAS) from baseline to 15, 60, 120 and 240 min and four-hourly thereafter in patients with “confirmed renal colic” and with “suspected renal colic” will be compared between the two trial arms at each time point using the Mann-Whitney *U* test, and across all time points using repeated measures ANCOVA including the baseline pain scores as a covariate, along with any other clinical/demographic covariates of import.

The change in pain scores (measured with the McGill Pain Questionnaire) from baseline to 15, 30, 60 and 120 min in patients with “confirmed renal colic” and with “suspected renal colic” will be compared between the two trial arms at each time point using the Mann-Whitney *U* test and across all time points using repeated measures ANCOVA including the baseline pain scores as a covariate, along with any other clinical/demographic covariates of import.

#### Clinical outcomes

Secondary continuous outcomes (length of stay, degree of hydronephrosis) will be compared between the two treatment groups using the Mann-Whitney *U* test. Secondary categorical outcomes (frequency and dose of morphine, other analgesics required, and presence, site and size of renal calculus) will be compared between the two treatment groups using the chi-squared test.

#### Feasibility outcomes

Descriptive statistics will be presented to summarise the feasibility outcomes across each of the randomisation groups, where relevant. The continuous feasibility outcomes will be reported with medians and interquartile ranges (IQR), whilst the categorical feasibility outcomes will be reported with frequencies and percentages.

#### Patient Satisfaction Questionnaire

Frequencies and percentages will be used to report the responses in the patient satisfaction questionnaire by treatment group and will be compared using a chi-square test.

#### Toxicity

The number and percentage of patients reporting a SAE or SUSAR will be summarised by treatment group and compared using a chi-square test.

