
Expert advice has already been sought on the route of drug delivery from both a phase II trial methodologist ([name], Liverpool CTU) and a Professor of Drug Discovery ([name], University of Nottingham).

Intravenous salbutamol is the IMP for this phase II trial. Inhaled salbutamol is certainly a feasible option (and will likely form part of the phase III trial design), but for the purposes of this phase II trial, it was felt important to maximise bioavailability and reduce confounding factors in terms of absorption in order to ensure maximal safe serum levels such that any potential efficacy signal on the primary endpoint is apparent.

This trial represents a re-purposing of an established treatment. We have therefore employed the established maximum safe and efficacious intravenous dose used for acute exacerbations of asthma; this dose is safe for patients who meet the inclusion criteria [11]. A higher dose is possible but is associated with a greater frequency of side effects [11]; this dose is employed in pregnant women in pre-term labour where the potential benefits outweigh the potential harms.

The frequently occurring side effects of tremor and tachycardia are very well tolerated by the majority of patients and were felt by our patient group to be acceptable if salbutamol is proven to be an effective analgesic. Patients with ischaemic heart disease tolerate tachycardia less well and for this reason are excluded from this trial. Rare occurrences of myocardial ischaemia with the use of high doses of salbutamol have been identified [11]. The dose being administered in this trial is the typical “loading” dose of intravenous salbutamol used when patients are having an acute, severe and/or life-threatening asthma attack. Such patients have typically already received large doses of inhaled beta-agonist in addition to this intravenous dose. It is therefore not thought that the proposed dose poses a significant risk in patients without known ischaemic heart disease.

The dose and rate of administration chosen are the same as that for the relief of severe bronchospasm: 250 μg diluted to a total volume of 5 ml with 0.9% sodium chloride and given by slow intravenous injection over 3–5 min [11, 27].

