Salbutamol is known to precipitate hypokalaemia [11]. The literature assessing the magnitude of this effect suggests a drop of 0.87–1.4 mmol/l [28] with a bolus dose of intravenous salbutamol. However, this trial data is largely obtained in patients with underlying hyperkalaemia, and it would appear that the lower the baseline serum potassium, the smaller the drop seen with intravenous salbutamol. Additionally, the doses used in studies identified in the review paper referenced use a higher dose of salbutamol than this trial protocol dictates. Finally, 40% of patients identified in the review paper were non-responders to salbutamol, i.e. intravenous salbutamol did not cause a fall in serum potassium. As such, we feel the potential side effect of hypokalaemia secondary to a single bolus dose of intravenous salbutamol is likely to be clinically insignificant. However, we dictate that serum potassium must be ≥ 3.7 mmol/l for a participant to be eligible for enrolment. Symptomatic hypokalaemia secondary to trial medication will be recorded as an adverse reaction.

Risks surrounding cannulation of the patient, taking of blood samples and preparation of the trial medication are covered by existing nursing staff training and procedures and provide no additional risk above normal patient care.

This trial is categorised as follows:

Type A = No higher than the risk of standard medical care—the trial involves the use of a medicinal product licenced in an EU member state, used for an off-label indication, supported by extensive clinical experience with the product and no reason to suspect a different safety profile in the trial population [29].

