### Methods for additional analyses (e.g. subgroup analyses) {20b}

At randomisation, the final diagnosis of the recruited participants is unknown, and hence, we randomise all participants with “suspected renal colic”. However, this is a phase II efficacy trial, and the primary group of interest is the patients with “confirmed renal colic”, which is a diagnosis that we know at participant’s discharge. Therefore, the primary analysis of the primary endpoint will be carried out within the “confirmed renal colic” group on the full data set, which will be defined on the “modified” intention-to-treat principle retaining patients in their initially randomised groups irrespective of any protocol violations. Analyses of the “suspected renal colic” and the “other diagnosis” groups for all secondary endpoints will also be done on the “modified” intention-to-treat principle.

Secondary analysis of the primary endpoint will be carried out within the “confirmed renal colic” and “suspected renal colic” groups on the per-protocol principle by excluding any patients with major protocol deviations. In addition, the analysis of the primary endpoint will be undertaken on the “as treated” principle by including patients in the treatment group of the actual medication they have received.

Analysis of harms (adverse events) will be restricted to participants who received the allocated trial medication, so that absence or occurrence of harm is not attributed to a treatment that was never received.

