#### Adverse event reporting and harms {22}

The use of salbutamol is outside of its licenced indication, but with a well-known safety profile and no reason to suspect a change in the safety profile for the population of patients included in the trial. For this trial, it is expected that all adverse events (AEs) that show a potential causal relationship with the IMP, known as adverse reactions (ARs), are recorded. Other AEs of unexpected severity (in the opinion of the investigator), or which meet the criteria for a serious adverse event (SAE) should also be recorded. They should be recorded using the CTCAE term provided in the NCI CTCAE v5.0. Severity should be assessed using the NCI CTCAE v5.0 grading. The clinical course of each event should be followed until resolution or stabilisation.

Events that are recognised, and expected complications of renal colic are not required to be reported as adverse events unless they are of an unexpected severity (i.e. require an intervention not usually required in the management of renal colic and its complications), are thought to be related to the IMP (and are therefore ARs) or meet the definition of serious.

The following circumstances are usually not considered SAEs:
Routine treatment or monitoring of the studied indication not associated with any deterioration in conditionTreatment which was elective or pre-planned for a pre-existing condition not associated with any deterioration in conditionAny admission to a hospital or other institution for general care where there was no deterioration in conditionTreatment of an emergency on an outpatient basis for an event not fulfilling any of the definitions of serious as given above and not resulting in hospital admission

All AE/ARs and SAE/SARs (not considered exempt) must be recorded from the time of trial medication administration until the end of the participant’s last data collection. Due to the fast-acting nature and short half-life of salbutamol, active monitoring for AEs and ARs is not required after 2 h post-administration. Following this, investigators are still required to record any ARs or SARs they become aware of.

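### The stated harms comparison covers only SAEs and SUSARs, tested by chi-square, and leaves out the side effects that are a listed secondary outcome

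*Protocol article*

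**What the plan says.** The Toxicity section is one sentence: "The number and percentage of patients reporting a SAE or SUSAR will be summarised by treatment group and compared using a chi-square test".

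Other parts of the protocol article bear on it:

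- **Secondary endpoints/outcomes** lists side effects of the trial treatment as an outcome in its own right.
- **Adverse event reporting and harms {22}** asks that all events with a potential causal link to the study drug, "known as adverse reactions (ARs), are recorded", with CTCAE v5.0 terms and grades.
- **Potential benefits** says: "The frequently occurring side effects of tremor and tachycardia are very well tolerated by the majority of patients". It also makes symptomatic hypokalaemia due to trial medication a recorded adverse reaction.
- **Table 1** has heart rate at baseline, 15, 30, 60 and 120 min.
- **Clinical outcomes** names the categorical outcomes to be tested: "Secondary categorical outcomes (frequency and dose of morphine, other analgesics required, and presence, site and size of renal calculus"). Side effects are not among them.
- **Methods for additional analyses {20b}** gives a harms population: "Analysis of harms (adverse events) will be restricted to participants who received the allocated trial medication". It names no summary and no contrast.

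On timing, Table 1 marks adverse event assessments at 4, 8, 12, 16, 20 and 24 h, while section {22} says "active monitoring for AEs and ARs is not required after 2 h post-administration".

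**The concern.** The Toxicity section does more than stay silent on detail. It fixes an endpoint (SAE or SUSAR) and a test (chi-square), and the endpoint is narrower than the listed secondary outcome it would be expected to serve. A statistical analysis plan that followed it literally would test serious events and need not compare adverse reactions at all.

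This matters because tolerability is part of the protocol's own case for salbutamol: Potential benefits lists a better side effect profile as one of the gains. A later phase III trial needs to know how much more tremor and tachycardia the drug causes than placebo, with an interval. If the comparison of serious events is the only one reported, a non-significant result on a handful of events could be taken for reassurance that it cannot give.

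**Working it through.** **Inputs from the protocol article**

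- 53 patients with confirmed renal colic per arm (Sample size), so 2 × 53 = 106.
- About 30% of suspected cases have no calculus, and about 152 are to be recruited (Recruitment).
- 1:1 allocation (Trial design).

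The recruitment figure reproduces: 106 / (1 − 0.30) = 151.4, rounded up to 152, which is 76 per arm. Harms are assessed in everyone treated, so 76 is the relevant number.

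**Inputs assumed.** The document gives no SAE rate and no adverse reaction rate. SAE rates of 0.5% to 5% and the adverse reaction rates below are assumptions.

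**Expected counts.** Expected patients with an SAE per arm = 76 × rate. Chance of none in either arm = (1 − rate)^152. The actual size is that of the nominal 5% Pearson chi-square test, by exact binomial enumeration.

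| Assumed SAE rate, both arms | Expected per arm | Chance of no SAE at all | Actual size |
|---|---|---|---|
| 0.5% | 0.4 | 47% | 0.1% |
| 1% | 0.8 | 22% | 0.7% |
| 2% | 1.5 | 5% | 2.9% |
| 3% | 2.3 | 1% | 4.3% |
| 5% | 3.8 | under 0.1% | 4.9% |

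An expected count of 5 per arm needs a rate of 5 / 76 = 6.6%.

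**What chi-square does with such tables.** For 4 versus 0 among 76 per arm, the pooled proportion is 4 / 152 = 0.0263. Then χ² = (4/76)² / [0.0263 × 0.9737 × (2/76)] = 4.11, p = 0.043. Fisher's exact test gives p = 0.12. For 5 versus 0 the two p-values are 0.023 and 0.058. In both cases the verdict at 5% depends on the choice of test.

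**Power, by exact enumeration at 76 per arm**

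| Events | Assumed rates | Pearson chi-square | Fisher |
|---|---|---|---|
| SAE | 1% vs 3% | 9.4% | 1.3% |
| Adverse reaction | 5% vs 20% | 83% | 77% |
| Adverse reaction | 5% vs 25% | 96% | 93% |

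Under these assumptions, the same participants give little information on serious events and a good deal on common reactions.

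**The case against.** The strongest reply is that this is a condensed article, that a separate statistical analysis plan is promised, and that tables of adverse reactions by term and grade are routinely left to such a plan. Section {20b} does speak of analysing all secondary endpoints, which include side effects, and of an analysis of adverse events with its own population. A reader might infer from the Toxicity section that side effects will go unanalysed. The documents do not support that: the method is unnamed, not ruled out. What remains is that the one section that does name a harms comparison limits it to serious events.

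Three other strong readings also go too far.

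- **That chi-square is invalid here.** Its actual size stays below 5% at every rate tabulated, so there is no excess of false positives. It is unreliable in sparse tables, as the split verdicts show.
- **That SAE counts are bound to be near zero.** This is an inference. It is well grounded for SUSARs and for drug-related SAEs, given a single dose and the risk category "Type A = No higher than the risk of standard medical care". It is weaker for all SAEs, because complications of renal colic remain reportable when serious.
- **That ending active monitoring at 2 h biases the comparison.** Section {22} still requires later adverse reactions that come to the investigator's attention to be recorded, and assessment is blinded in both arms. No between-arm bias is shown. The mismatch with Table 1 is one of wording and follow-up window, and is minor.

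**Conclusion.** The point holds as a mismatch within the document: a listed secondary outcome, recorded and graded, has no place in the only harms comparison stated. That comparison is poorly suited to its data at any SAE rate below about 6.6%. For an assumed 1% versus 3%, its power is about 9% by Pearson chi-square as planned and about 1% by Fisher. Both are too low to detect or exclude anything useful, and the lower figure should not be attributed to the planned test. Adverse reactions at an assumed 5% versus 20% to 25% would have about 77% to 93% power by Fisher.

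The conclusion rests on 76 treated participants per arm and on assumed event rates. It does not touch the primary analysis, the sample size or the collection of safety data. It should be corrected, because the better analysis uses data that the trial already collects.

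**What to change.** Amend the Toxicity section and carry the change into the statistical analysis plan:

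1. Report, by medication received, the number and percentage of participants with any adverse reaction and with each main expected one (tremor, tachycardia or palpitations, symptomatic hypokalaemia) over the actively monitored 0 to 120 min. Give risk differences with exact 95% confidence intervals, and Fisher's test if a test is wanted. Grouping by medication received serves the aim in section {20b} of not attributing harm to a treatment that was never given.
2. Summarise heart rate by arm at the scheduled times to 120 min.
3. List SAEs and SUSARs by arm descriptively, or use an exact method in place of chi-square.
4. Reconcile the adverse event assessments at 4 to 24 h in Table 1 with section {22}, so that the reporting window is unambiguous and events noted after 2 h are presented as passively recorded if that is what is meant.

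The cost is some wording and a few more tables. Recruitment, sample size and data collection for items 1 to 3 are unchanged.

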### Interim analyses {21b}

No formal interim analysis is planned, but the sponsor and funder reserve the right to discontinue this trial at any time for ethical, safety or any other administrative reason. If this occurs ,the sponsor shall justify its decision in writing and will promptly inform any relevant parties (i.e. investigators, participating sites, REC, regulatory bodies).

The sponsor and funder shall take advice from the Trial Steering Committee as appropriate in making this decision. An independent Data Monitoring and Ethics Committee shall monitor accumulating data and oversee safety issues. The reporting requirements and frequency of reports will be defined in the TSC and DMEC Charters.

The DMEC will advise the TSC if, in its view, there are any ethical or safety issues that may necessitate the closure of the trial. These issues include (but are not limited to) the following:
Prevalence of excess side effects, SARs or SUSARs in the intervention group deemed unacceptable as defined by the DMEC

### Methods for additional analyses (e.g. subgroup analyses) {20b}

At randomisation, the final diagnosis of the recruited participants is unknown, and hence, we randomise all participants with “suspected renal colic”. However, this is a phase II efficacy trial, and the primary group of interest is the patients with “confirmed renal colic”, which is a diagnosis that we know at participant’s discharge. Therefore, the primary analysis of the primary endpoint will be carried out within the “confirmed renal colic” group on the full data set, which will be defined on the “modified” intention-to-treat principle retaining patients in their initially randomised groups irrespective of any protocol violations. Analyses of the “suspected renal colic” and the “other diagnosis” groups for all secondary endpoints will also be done on the “modified” intention-to-treat principle.

Secondary analysis of the primary endpoint will be carried out within the “confirmed renal colic” and “suspected renal colic” groups on the per-protocol principle by excluding any patients with major protocol deviations. In addition, the analysis of the primary endpoint will be undertaken on the “as treated” principle by including patients in the treatment group of the actual medication they have received.

Analysis of harms (adverse events) will be restricted to participants who received the allocated trial medication, so that absence or occurrence of harm is not attributed to a treatment that was never received.

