#### Criteria for discontinuing or modifying allocated interventions {11b}

Each participant will receive a single dose of the allocation intervention, and dose modifications are not permitted. If a participant develops clinical evidence of a significant adverse reaction during the administration of treatment, then this can be stopped at the direction of the treating clinician.

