## Discussion

The study remains ongoing but offered some logistical challenges identified during set-up which were addressed by the team.
The study’s limited funding meant that pre-filled syringes could not be provided for the team therefore a different strategy to maintain the blind was required. As the trial medication is made up in a department, and not by a separate pharmacy, non-research team members are required to make up either the IMP or placebo and provide in a blinded syringe for the research team to administer. Designated members of a separate research team, not working on this trial, will be unblinded and support the SARC research team and R&D Pharmacy team in monitoring drug accountability and re-ordering stock for the department. No one with knowledge of a participant’s allocation will be involved in data collection or patient monitoring for the trial.Further to this, as non-research staff members will be randomising patients, a simple randomisation system was required that avoided the need for an additional log in or access to a computer as is the case with online randomisation systems. Building on work done in the Rapid Analgesia for Prehospital Hip Disruption (RAPID) study (ref) using scratch cards for concealment allocation, we decided to implement this as a simple method of randomisation for the SARC trial. We will monitor randomisation adherence and intend to report back on this alongside user acceptability in a separate study.

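### The harms rule, read as written, removes anyone given the other arm's syringe from the comparative harms analysis; grouping by drug received would keep them

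*Protocol article*

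**What the plan says.** Three statements in the protocol article bear on who is counted for harms.

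- **Methods for additional analyses {20b}, harms.** "Analysis of harms (adverse events) will be restricted to participants who received the allocated trial medication". The reason follows directly: "so that absence or occurrence of harm is not attributed to a treatment that was never received".
- **Same section, efficacy.** Just before the harms sentence, the article provides that "the analysis of the primary endpoint will be undertaken on the “as treated” principle by including patients in the treatment group of the actual medication" received. Here, participants who got the wrong drug are kept and reclassified.
- **Toxicity.** "The number and percentage of patients reporting a SAE or SUSAR will be summarised by treatment group and compared using a chi-square test". The article does not say whether the treatment group here is the one allocated or the one received.

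Side effects of trial treatment also appear in the list of secondary outcomes. Section {20b} assigns the analyses of all secondary endpoints in the suspected-colic and other-diagnosis groups to a modified intention-to-treat set, which keeps participants as randomised despite protocol violations.

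**The concern.** The harms sentence sets two conditions at once: the participant must have received trial medication, and it must have been the one allocated. The first is the usual basis of a safety population. The second removes a participant whose exposure is real and known but differs from the allocation. Someone allocated placebo and given salbutamol is a salbutamol exposure, yet would appear in neither column of the harms table.

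Wrong syringes are possible in this trial. Pre-filled syringes could not be funded, and the Discussion explains that "non-research team members are required to make up either the IMP or placebo and provide in a blinded syringe for the research team to administer". The two syringes look identical, so the person injecting cannot see a mistake. The article itself foresees the problem, because it plans an as-treated analysis of the primary endpoint. What is at stake is whether the harms comparison, which will inform the phase III decision, reflects actual exposure.

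**Working it through.** **1. Who the rule keeps and who it drops**

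| Allocated | Received | Harms rule in {20b} | Grouped by drug received |
|---|---|---|---|
| Salbutamol | Salbutamol | Kept, salbutamol | Kept, salbutamol |
| Placebo | Placebo | Kept, placebo | Kept, placebo |
| Placebo | Salbutamol | Dropped | Kept, salbutamol |
| Salbutamol | Placebo | Dropped | Kept, placebo |
| Either | Nothing | Dropped | Not in the set; listed separately |

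The stated reason is satisfied in every row of the last column: no harm is assigned to a drug that was not given. The two columns differ only in the wrong-syringe rows. Excluding a participant under the present rule already requires knowing that the syringe was the wrong one. In a two-arm trial that same knowledge is enough to place them in the correct group.

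**2. Does any other section bring them back?**

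- *Toxicity* refers only to treatment group and defines no analysis set.
- *Adverse event reporting and harms {22}* governs recording and reporting, not the comparative analysis.
- The modified intention-to-treat rule for secondary endpoints could be read to cover the side-effects outcome. It would, however, count a wrong-syringe participant under the allocated drug, which is the misattribution the harms sentence sets out to avoid. The two rules give different sets for the same kind of data.

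No section classifies harms by drug received.

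**3. Scale**

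Inputs from the article: 53 confirmed cases per arm (Sample size {14}); about 30% of recruits without a calculus (Recruitment {15}); 1:1 allocation (Trial design {8}).

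The article's total is reproduced: 2 × 53 = 106, and 106 / (1 − 0.30) = 151.4, rounded up to 152. At 1:1 this is 152 / 2 = 76 per arm.

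Assumption: a wrong-syringe rate *w*, equal in both arms. The article gives no rate.

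- Excluded in total = 152 × *w*
- Placebo-arm salbutamol exposures excluded = 76 × *w*
- Salbutamol exposures left in the analysis = 76 × (1 − *w*), against 76 when grouped by drug received

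| *w* | Excluded in total | Of these, salbutamol exposures in placebo arm | Salbutamol exposures analysed |
|---|---|---|---|
| 1% | 1.5 | 0.8 | 75.2 |
| 2% | 3.0 | 1.5 | 74.5 |
| 5% | 7.6 | 3.8 | 72.2 |

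With grouping by drug received, the number excluded for this reason is 0 at any *w*.

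To illustrate with a single swap: if one placebo-arm participant receives salbutamol and has the only event of its kind, the salbutamol risk is 1/77 (1.3%) by drug received and 0/76 under the present rule.

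**The case against.** The best defence is the purpose clause. It reads like an ordinary treated-population rule aimed at people randomised but never dosed, loosely worded in a condensed article. The authors may well have meant participants who received trial medication. That is plausible, but the sentence says allocated, and an analysis plan that follows it literally will drop the wrong-syringe cases.

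Three stronger readings are tempting and are not supported:

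- **That these participants vanish from safety oversight.** They do not. Section {22} requires events to be recorded from administration of trial medication, with no condition on correct allocation. SUSAR reporting and committee review of safety data likewise carry no such condition.
- **That participants whose injection was stopped early are excluded.** Section {11b} says: "If a participant develops clinical evidence of a significant adverse reaction during the administration of treatment, then this can be stopped". Such a participant did receive allocated medication in part, and the harms sentence does not require a full dose. This reading is strained.
- **That harm is systematically understated.** What remains is accidental swaps, which can run in either direction. Nothing in the article links them to outcome.

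It is also fair to say that nothing suggests swaps are common. Each participant gets one dose, cards are drawn in order from a dispenser, delegated unblinded staff prepare the syringe, accountability is recorded on the card, and randomisation adherence is monitored.

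**Conclusion.** The point holds for the final comparative analysis of harms and for wrong-syringe recipients only. As worded, the rule excludes known exposures to no purpose, since grouping by drug received meets the stated aim in full and is already planned for the primary endpoint.

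The size is unknown and probably small: about 2 to 8 of 152 participants, including about 1 to 4 placebo-arm salbutamol exposures. This rests on an assumed wrong-syringe rate of 1% to 5%, equal in both arms; the true number may be none. The efficacy analysis, the sample size, event capture and expedited reporting are untouched. It should be fixed, but it is not a critical flaw.

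**What to change.** Replace the harms sentence in {20b} with: *Harms will be analysed in all participants who received any amount of trial medication, grouped by the medication actually received.* The words on any amount also settle doubt about partly given injections.

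Apply the same set to the SAE/SUSAR comparison under Toxicity and to the side-effects item in the secondary outcomes, and state that the modified intention-to-treat rule does not govern those two. List participants who received no trial medication separately.

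The cost is one replaced sentence and two cross-references. Drug accountability is already recorded on the back of each scratch card {11c}, so no new data collection appears to be needed. Make the change before the unblinded analysis, so that the safety set is not chosen with the events in view.
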